## Abstract

**Background:**

Information on the prevalence of adjustment disorders among cancer patients and the value of psychological interventions in this group of patients is limited. This study investigates the prevalence of adjustment disorders among cancer patients as well as the reach, effectiveness, cost-utility and budget impact of a tailored psychological intervention.

**Method:**

This study consists of two parts. Part 1 is an observational study among a representative group of mixed cancer patients after cancer treatment on the prevalence of adjustment disorder as well as the uptake (i.e. reach) of psychological treatment. In Part 2, patients diagnosed with an adjustment disorder are invited to participate in a randomized controlled trial. Patients will be randomized to the intervention (access to the tailored psychological intervention) or control group (waitlist period of 6 months). The psychological intervention consists of three modules: one module containing psycho-education (3 sessions, all patients) and two additional modules (maximum of 6 sessions per module) provided as continuum, in case needed. Module 2 and 3 can consist of several evidence-based interventions (e.g. group interventions, mindfulness, eHealth) The primary outcome is psychological distress (HADS). Secondary outcomes are mental adjustment to cancer (MAC) and health-related quality of life (EORTC QLQ-C30). To assess the cost-utility and budget impact, quality of life (EQ-5D-5 L) and costs (iMCQ and iPCQ) will be measured. Measures will be completed at baseline and 3 and 6-months after randomization.

**Discussion:**

This study will provide data of the prevalence of adjustment disorders and the reach, effectiveness, cost-utility and budget impact of a tailored psychological intervention.

**Trial registration:**

Netherlands Trial Register identifier: NL7763. Registered on 3 June 2019.

## Background

Worldwide the incidence of cancer is growing. It was estimated that 18.1 million people worldwide were newly diagnosed with cancer in 2018 [1]. There is convincing empirical evidence that cancer patients have to deal with a wide range of physical symptoms and psychological, social and existential problems related to cancer and its treatment, both during treatment and at (long-term) follow-up. Psychological problems involve symptoms related to anxiety and depression, but also problems with adjustment to cancer and its sequelae [2]. In case of severe and persistent problems with adjustment to cancer, an adjustment disorder can be diagnosed according to the Diagnostic and Statistical Manual of Mental Disorders (DSM-V) [3]. An adjustment disorder is characterized by symptoms such as anxiety, depression or fatigue and can be developed in case of insufficient protective factors (e.g. resilience or meaning making), which can result in significant impairments in a patients’ life (e.g. work or study, social relations or emotional problems) [3].

Earlier studies showed prevalence rates of adjustment disorder varying from 6% to over 19%, as measured using diagnostic interviews. In a meta-analysis of Mitchell et al. (2011) [4] the prevalence of adjustment disorder among cancer patients was estimated to be 19%, while in more recent studies somewhat lower prevalence rates of 6 to 17% were reported [5–8]. In a recent large study in Germany of Mehnert et al. (2014) [7] in a population of mixed cancer patients who had their cancer diagnosis for on average 13.5 months, 11% of all patients had an adjustment disorder in the previous 4 weeks (independently of other psychological disorders such as anxiety or depression).

In case an adjustment disorder is diagnosed, evidence or practice based psychological interventions should be available and provided to the patient [3]. However, in clinical practice, psychological treatment is often not optimally accessible for cancer patients, especially for those with an adjustment disorder. Several bottlenecks in the organization of psychological treatment have been identified, including problems with identifying cancer patients with an adjustment disorder, and problems with referral to psychological treatment [9–13]. In addition, when an adjustment disorder is diagnosed in cancer patients, the accessibility of psychological care is limited, since there is currently no adequate coverage and reimbursement of adjustment disorders treatments in cancer patients after active cancer treatment [14].

A systematic review of Faller et al. (2013) [15] and several studies published after the conduction of this review [16–24] showed evidence for the effectiveness of psychological interventions targeting cancer patients, including self-management interventions, eHealth interventions, group interventions, and individual interventions. Also, two reviews showed that psychological interventions targeting cancer patients are likely to be cost-effective at potentially acceptable willingness-to-pay thresholds [25, 26]. Three recent cost-utility studies, on meaning-centred group psychotherapy, stepped psychological care, and blended cognitive behavioural therapy, even showed that psychological treatment is more effective and potentially less costly compared to care-as-usual [16, 27, 28]. However, to the best of our knowledge, no study specifically focused on the effectiveness, cost-utility and budget impact of psychological interventions in cancer patients with an adjustment disorder.

This randomized controlled trial, therefore, aims to provide insight into the prevalence of an adjustment disorder among cancer patients, and the reach, effectiveness, cost-utility and budget impact of a tailored psychological intervention. The results are relevant to improve care (including accessibility and reimbursement) for cancer patients with an adjustment disorder.

## Methods

The methods section of this study protocol is written in accordance with the STROBE statement for cohort studies and CONSORT statement for reporting randomized controlled trials (RCT) [29, 30].

### Study design

This study consists of two parts. Part 1 is an observational study among a representative group of cancer patients after medical treatment in which the prevalence of an adjustment disorder as well as the uptake of psychological treatment (i.e. reach) is assessed. Part 2 includes an RCT in which the effectiveness, cost-utility and budget impact of a tailored psychological intervention compared to waitlist control care is investigated. The patient flow through the study is shown in Fig. 1 and the schedule of enrolment, assessments and interventions is provided in Fig. 2. This study has been approved by the Medical Ethical Committee of the VU University Medical Center.

**Fig. 1 Fig1:**
[figure not shown]
Study design of part 1 and 2 combined with expected number of patients per step

**Fig. 2 Fig2:**
[figure not shown]
Standard protocol items as highly recommended according the SPIRIT

### Part 1: study population and inclusion procedure

For Part 1 of this study, we aim to screen a representative group of mixed cancer patients on the prevalence of an adjustment disorder. Participants will be included in this study in case they are diagnosed with cancer (all types and stages, except non-melanoma skin cancer) before July 2018, finished cancer treatment with curative or palliative intent (all treatment modalities, except for endocrine therapy in breast/prostate cancer) and are aged ≥18 years. A random selection will be drawn by the Netherlands Cancer Registry (NCR) of patients from participating departments of participating hospitals. The NCR registers all newly diagnosed cancer patients within 6 months after diagnosis in the Netherlands. The patient information letter will be sent by post to the eligible patient by the former treating physician. When a patient is willing to participate, he or she is asked to provide informed consent. All data will be collected using the Patient Reported Outcomes Following Initial treatment and Long-term Evaluation of Survivorship (PROFILES) system. PROFILES is a registry and is directly linked to data of the NCR. All necessary permissions were obtained to access and use the data and who gave this permission.

### Part 1: prevalence and reach

The prevalence of adjustment disorder diagnosis will be investigated using a two-step approach. First, patients will be screened on the increased risk for an adjustment disorder using a set of screening questionnaires. Patients will be asked to complete these questionnaires online or via paper-and-pencil. The screening questionnaires consist of the distress thermometer (DT), the problem list and the Hospital Anxiety and Depression Scale (HADS). The DT measures the level of distress experienced in the last week on a thermometer ranging from 0 (no distress) to 10 (extreme distress) [31]. The problem list measures 47 different problems, including practical problems, family/social problems, emotional problems, spiritual/religious concerns, physical problems and a free-text section on any additional problems on a dichotomous scale (Yes/No), as well as a single item on wanting to talk to a psychologist, psychotherapist or psychiatrist. All items refer to ‘last week’. The HADS includes 14-items measuring psychological distress (HADS-T), anxiety and depression as further discussed below [32]. In addition, patients will be asked to complete the Checklist Individual Strength (CIS) and questions on sociodemographic (e.g. marital status, living situation, education level, employment status) and clinical characteristics (e.g. tumour recurrence). The CIS consists of 20 items (7-point Likert scale) on subjective experiences of fatigue, concentration, motivation, and physical activity [33]. The CIS which strongly resembles the multidimensional fatigue inventory (MFI) [34], has been shown to be a valid and reliable measurement to investigate fatigue with good internal consistency [35].

Second, patients with an increased risk for an adjustment disorder (i.e. HADS score > =11, DT > =4 or work/school/study problems, family or social problems, emotional problems, fatigue or wanting to talk to a psychologist or social worker as reported on the problem list) will be invited for a diagnostic interview by a registered psychologist, psychotherapist or psychiatrist trained in clinical care for cancer patients with an adjustment disorder (further called healthcare professional (HCP)). During this diagnostic interview by telephone or face to face the presence of an adjustment disorder will be investigated. HCPs will follow the Dutch guideline on adjustment disorder diagnosis [36]. The guideline committee recently defined adjustment disorder in patients with cancer as the combination and interaction among three pillars, namely stressors (e.g. cancer diagnosis, fear of cancer recurrence, physical changes in a patients’ appearance), insufficient protective factors (e.g. resilience, physical health, meaning, social support, autonomy), and the experience of symptoms (e.g. anxiety, depression, fatigue, relation problems, limited work productivity) [3]. During the diagnostic interview, the HCP will also complete a form on sociodemographic (age, gender) and clinical (tumour site, stage, phase of cancer (acute/chronic/palliative), time since diagnosis, treatment modality) parameters, and a form on stressors experienced, protective factors, symptoms experienced and actual psychologic diagnosis. To monitor the robustness of this diagnosis, the diagnostic interview will be audio recorded in case the patient provides specific informed consent on this matter. Approximately 5 % of the total diagnostic interviews will be scored twice (adjustment disorder yes/no).

Additionally, all participating HCPs will be asked to complete a questionnaire on type of care (primary or secondary care), profession and training, and years of experience in working with cancer patients.

### Part 2: study population and inclusion procedure

Patients diagnosed with an adjustment disorder in Part 1 of this study will be invited to participate in Part 2 (the RCT). Patients will be first introduced to the study by the HCP. The coordinating researcher of the study will further inform interested patients by phone. Also, the patient information form and informed consent of Part 2 will be sent to the patient. After obtaining informed consent, the patient is asked to fill in the baseline questionnaire via the internet or using paper-and-pencil. After completing the baseline questionnaire, the patient will be randomized into either the intervention group (start of the tailored psychological intervention within 3 a 4 weeks) or the waitlist control group (receive a tailored psychological intervention after a waitlist period of 6 months). All patients will be asked to complete questionnaires before randomization (T0), and 3 (T1) and 6 months (T2) after randomization. In case of non-response to these questionnaires a reminder letter and a paper-and-pencil questionnaire will be sent after 3 weeks. If they do not respond to this reminder, they will be contacted by telephone within 2 weeks. Reasons for dropouts will be registered. Data will be collected using the PROFILES system.

### Part 2: tailored psychological intervention

The psychological intervention investigated in this proposed project follows the Dutch guideline on diagnosis of adjustment disorders [36] and consists of 3 modules. Module 1 encompasses a maximum of 3 sessions on psycho-education with an HCP. Module 2 and 3 encompass both a maximum of 6 sessions. Module 2 and 3 can consist of all evidence-based interventions outlined in the guideline on adjustment disorders, such as cognitive behavioural therapy, mindfulness, group interventions, online interventions or pharmacotherapy [3]. Depending on the wishes and needs of the patient a specific type of therapy per module will be offered to the patient (tailored treatment) [37].

After each last session of a module the HCP will assess in accordance with the patient if another module is needed. To support this assessment the patient will complete the HADS during this session, following the guideline on diagnosis of adjustment disorders [36]. When sufficiently effective, only the short psychological treatment module 1 will be provided. The longer treatments (module 2 or module 3) will only be offered if the previous psychological treatment module was insufficiently effective, so the 3 modules will be provided as a continuum.

### Part 2: control group

Patients randomised to the waitlist control group receive the tailored psychological intervention after a waitlist period of 6 months. This period is comparable with the usual waitlist period for psychological care in the clinical practice. During the waitlist period it is allowed to receive usual care. Usual care received during the study will be measured using the healthcare utilization questionnaire discussed below.

### Part 2: randomization

Randomization will be conducted centrally by an independent person in blocks of four and six using an automatically created randomisation list. Randomization will be stratified for the patient self-reported prognosis and severity of psychological distress by an independent person. Patients are not blinded to treatment allocation. Data managers will be blinded to the treatment allocation.

### Part 2: outcome assessments

The primary outcome of Part 2 is psychological distress. Secondary outcomes are Mental Adjustment to Cancer and health-related quality of life. In addition, the cost-utility and budget impact of the psychological intervention will be investigated (Table 1). To determine cost-utility and budget impact, Quality-Adjusted Life-Years (QALYs) and costs will be measured. For the cost-utility and budget impact analyses from a societal perspective, intervention costs, healthcare costs, costs of the patient and his/her family (e.g. informal care costs and travel costs) and costs in other sectors (e.g. productivity losses) will be collected. The healthcare perspective will only include intervention costs and healthcare costs and the insurer perspective will only include costs reimbursed by the healthcare insurance company.

**Table 1 Tab1:** Outcome measures and used instruments

Part	Outcome	Outcome measure	Instrument
1	Primary outcome	Reach: prevalence of adjustment disorder (yes/no) and uptake of the tailored psychological intervention (yes/no)	Screening (DT, problem list and HADS) and interview
1	Other collected measurements	Fatigue	CIS
2	Primary outcome	Psychological distress	HADS
2	Secondary outcomes	Mental adjustment to cancer	MAC
		Health-related quality of life	EORTC-QLQ-C30
		Cost-utility measures	
		Medical utilization costs Informal care costs	iMCQ questionnaire iMCQ questionnaire
		Productivity losses	iPCQ questionnaire
		Quality adjusted life-years	EQ-5D-5 L
1–2	Other collected measurements	Socio-demographic and clinical characteristics	Study specific questionnaire
		Healthcare professional characteristics	Short questionnaire on type of care

*HADS* Hospital Anxiety and Depression Scale, *CIS* Checklist Individual Strength, *MAC* Mental Adjustment to Cancer, *EORTC QLQ-C30* European Organization for Research and Treatment of Cancer Quality of Life Questionnaire, *iMCQ* Medical consumption questionnaire, *iPCQ* Productivity cost questionnaire, *HCP* healthcare professional

#### Primary outcome measures

Psychological distress will be measured with the HADS. The HADS is a 14-item (4-point Likert scale) patient-reported outcome measure for measuring psychological distress, anxiety and depression [32]. All items refer to the last week. The total HADS (HADS-T) score ranges from 0 to 42. A higher score indicates higher levels of distress. The HADS is a valid instrument for use in cancer patients and Dutch persons [38].

#### Secondary outcome measures

Cognitive and behavioural response to cancer diagnosis and treatment will be assessed using the 40-item (4-point Likert scale) Mental Adjustment to Cancer (MAC) questionnaire. The MAC scale comprises five subscales: fighting, spirit, helplessness/hopelessness, anxious preoccupation, fatalism and avoidance [39]. All items refer to the current situation. A higher score on the subscales indicate more fighting spirit, helplessness/hopelessness, anxious preoccupation, fatalism or more avoidance [40, 41]. Besides, based on these five sum scores, two summary scores can be calculated, namely positive adjustment (17 items) and negative adjustment (16 items). Psychometric characteristics of the MAC have previously been investigated among mixed cancer patients, including Dutch cancer patients [41].

Health-related quality of life will be measured with the 30-item (4-point Likert scale) European Organization for Research and Treatment of Cancer Quality of Life Questionnaire Core (EORTC QLQ-C30). This questionnaire consists of a global health-related quality of life scale, five functional scales (physical functioning, role functioning, emotional functioning, cognitive functioning and social functioning), three symptom scales (nausea and vomiting, fatigue and pain) and 6 single items relating to dyspnoea, insomnia, loss of appetite, constipation, diarrhoea and financial difficulties [42, 43]. All scales and single items can be converted to a score from 0 to 100. A higher score on the functioning scales or the global quality of life scale represents a better quality of life, whereas a higher score on the symptom scales or the single items indicate a higher level of symptoms. The EORTC QLQ-C30 is a valid and reliable instrument for health-related quality of life assessments in various cancer populations [42, 43].

Other outcomes as socio-demographic and clinical parameters and HCP characteristics are similar to the already collected measurements in Part 1 of this study.

#### Outcome measures on cost-utility and budget impact

Costs will be measured by questionnaires developed by the Institute for Medical Technology Assessments of the Erasmus University Rotterdam, as recommended in the Dutch Health Care Insurance Board (CVZ) guideline [44]. Healthcare utilization (e.g. visits to the general practitioner, visits to the medical specialist, and hospitalization) and received informal care will be assessed with the Medical Consumption Questionnaire (iMCQ) [45]. Losses due to absenteeism and presenteeism (decreased work productivity) will be assessed with the productivity cost questionnaire (iPCQ) [46]. In this study an adapted version of both questionnaires will be used with a recall period of 3 months.

QALYs will be calculated by multiplying the time spent in a specific health state with the quality (utility) of that health state. Utilities will be measured by using the EuroQol 5-demensions 5-item (5-point Likert scale) instrument (EQ-5D-5 L). The EQ-5D-5 L consist of five dimensions of quality of life (mobility, self-care, usual activities, pain/discomfort and anxiety/depression) [47]. The resulting profile of answers can be transformed to a value given by the general public: the EQ-5D index using the Dutch index tariff [48]. A visual analogue scale is also included, which represents the patients’ judgment of his own health state on a scale from 0 (worst health state) to 100 (best health state).

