For the cost-utility analyses, pertinent guidelines will be used [44]. Analyses will be conducted in agreement with the intention-to-treat principle from both a societal and healthcare perspective. Costs will be calculated by multiplying resource use by integral cost prices as presented in the cost guideline [44]. Productivity losses due to absenteeism and presenteeism will be calculated using the friction cost approach. Missing data on costs and utilities will be imputed using multiple imputation. The time horizon will be set at 6 months, and therefore neither costs nor effects need to be discounted. Incremental cost-utility ratios (ICURs) will be calculated with their 95% confidence intervals using 5000 bootstrap replications, which will be projected on a cost-utility plane. In addition, ICUR acceptability curves will be presented and sensitivity analyses will be performed focusing on uncertainty surrounding most important cost items.

For the budget impact analyses, the current guideline on budget impact analyses of the Dutch National health Care Institute (ZIN) and the International Society for Pharmacoeconomic and Outcomes Research will be used [44, 50]. To perform a budget impact analysis insight is needed on: a) size of the target population, b) costs of the intervention and 3) other costs (such as other healthcare costs). Several budget impact analyses will be performed, as this will provide insight into the uncertainty surrounding the budget impact of providing psychological treatment to patients with cancer with an adjustment disorder. Budget impact analyses will be performed from a healthcare (i.e. including intervention costs and healthcare costs), societal (i.e. including intervention costs, healthcare costs, costs of the patient and his/her family and costs in other sectors) and insurer perspective (i.e. including costs reimbursed by the healthcare insurance company).

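### The cost-utility analysis names no adjustment for baseline EQ-5D utility; adding one costs nothing and would make the QALY comparison more precise and less exposed to chance imbalance

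*Protocol article*

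**What the plan says.** Under Outcome measures on cost-utility and budget impact, the protocol article defines the effect measure: "QALYs will be calculated by multiplying the time spent in a specific health state with the quality (utility) of that health state". Utilities come from EQ-5D-5L, converted to "the EQ-5D index using the Dutch index tariff". The abstract gives the schedule: "Measures will be completed at baseline and 3 and 6-months after randomization". A baseline utility is therefore available for the analysis.

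Under Statistical analysis, the cost-utility paragraph opens with "For the cost-utility analyses, pertinent guidelines will be used" and then describes the steps. "Missing data on costs and utilities will be imputed using multiple imputation". On the horizon: "The time horizon will be set at 6 months, and therefore neither costs nor effects need to be discounted". On estimation: "Incremental cost-utility ratios (ICURs) will be calculated with their 95% confidence intervals using 5000 bootstrap replications". A cost-utility plane and acceptability curves follow. The sensitivity analyses it mentions concern cost items. No covariate is named for the QALY or the cost comparison.

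Under Part 2: randomization, the article says: "Randomization will be stratified for the patient self-reported prognosis and severity of psychological distress". Utility is not a stratification factor.

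**The concern.** The article sets out the route from utilities to ICUR in some detail, and none of the steps uses baseline utility as a covariate. Followed as written, the route compares mean QALYs between arms without adjustment. Part of each patient's QALY is then a value measured before randomisation, which treatment cannot change, and the 3- and 6-month utilities are likely to be correlated with it. Differences between patients at baseline therefore add noise to the comparison, and any chance difference between arms at baseline carries through to the incremental QALY.

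The effectiveness analysis differs here. The HADS model has arm, time and their interaction, so, if T0 is one of its time points, the effect is judged relative to baseline. The QALY comparison has no described counterpart.

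The cost-utility result matters because, according to Implementation and clinical practice, the study was requested to inform a reimbursement decision. Adding adjustment only after the baseline table has been seen would be open to criticism, so it is better fixed beforehand.

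**Working it through.** **The plan's own figures.** The only sample-size figures concern the HADS: difference 5, SD 11, power 80%, significance level 5% (taken as two-sided). The normal approximation gives 76 per arm and the t-test 76.95, so 77. Then 77 / 0.75 = 102.7, so 103 per arm. Both stated numbers reproduce. The article gives no figure for QALYs. I use 77 and 103 below to bracket the usable sample: 77 are expected at follow-up, and 103 would apply if imputation recovered everything.

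**Inputs from the article.** Utilities at 0, 3 and 6 months; horizon 0.5 year.

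**Assumptions, not in the article.** Straight lines between visits; equal variances at the three visits; the same correlation ρ between every pair of visits, taken as 0.3, 0.5 and 0.7; utility SD σ = 0.20 where an absolute size is needed.

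**QALY weights.** Each 3-month interval contributes 0.25 × (average of its two ends), so

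QALY = 0.125·u0 + 0.25·u3 + 0.125·u6.

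The weights sum to 0.5, and u0 carries 0.125 / 0.5 = 25%.

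**Variance, slope and R².**

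- Var(QALY) = σ²(0.09375 + 0.15625ρ). The first term is 0.125² + 0.25² + 0.125². The second is 2(0.125×0.25 + 0.125×0.125 + 0.25×0.125).
- Slope of QALY on u0 = 0.125 + 0.375ρ.
- R² = slope² / (0.09375 + 0.15625ρ).
- Adjusted SE / unadjusted SE = √(1 − R²).

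| ρ | Slope | R² | SE ratio | Interval narrower by |
|---|---|---|---|---|
| 0.3 | 0.2375 | 0.401 | 0.774 | 23% |
| 0.5 | 0.3125 | 0.568 | 0.657 | 34% |
| 0.7 | 0.3875 | 0.739 | 0.511 | 49% |

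These percentages depend on neither σ nor n.

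**Absolute SE of the QALY difference**, √(Var × 2/n), with σ = 0.20 and n = 77 per arm, unadjusted to adjusted: 0.0121 to 0.0094 (ρ = 0.3), 0.0134 to 0.0088 (ρ = 0.5), 0.0145 to 0.0074 (ρ = 0.7). With n = 103: 0.0116 to 0.0076 (ρ = 0.5) and 0.0126 to 0.0064 (ρ = 0.7).

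**Effect of a chance baseline gap.** One standard error of the baseline difference is 0.20 × √(2/n), which is 0.0322 for n = 77 and 0.0279 for n = 103. The expected shift in the unadjusted QALY difference is slope × gap:

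| ρ | n = 77 | n = 103 |
|---|---|---|
| 0.3 | 0.0077 | 0.0066 |
| 0.5 | 0.0101 | 0.0087 |
| 0.7 | 0.0125 | 0.0108 |

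Of each shift, 0.125 × gap (0.0040 and 0.0035 respectively) is purely arithmetic. The rest comes through the correlation with later utilities. The shift takes the sign of the gap. At n = 77, widening the assumptions to σ from 0.15 to 0.25 and ρ from 0.3 to 0.8 gives a range of about 0.006 to 0.017.

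**The case against.** The strongest reply is that the article is silent and has not made a choice. It never calls the comparison raw or unadjusted, and a bootstrap works equally well with a regression-adjusted difference in each replicate. It is a condensed account that defers to external guidelines, and the full protocol or a health-economic analysis plan may already name the covariates. This stands: a reader might infer that the trial has decided against adjustment, and the text does not support that. What remains is that the steps are described closely enough that someone following them would arrive at an unadjusted comparison.

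A reader might also fault the QALY definition. It is correct and would stay unchanged, because adjustment belongs to the comparison between arms.

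The size of the gain rests on assumed correlations with equal variances, which is why a range is shown; at a correlation of 0.3 it is still about 23%. The one-standard-error gap is computed as if allocation were unstratified. EQ-5D-5L has an anxiety/depression dimension, so stratifying on distress probably balances part of baseline utility, and real gaps may be somewhat smaller. The documents do not allow that reduction to be quantified.

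**Conclusion.** The point holds as a worthwhile improvement. No baseline adjustment is specified for the QALY comparison, although the covariate is collected and a quarter of the QALY weight sits on it under linear interpolation. The expected gain is an interval about 23% to 49% narrower for correlations of 0.3 to 0.7. It also protects against a shift of about 0.0066 to 0.0125 QALY per one-standard-error baseline gap (σ = 0.20, 77 to 103 per arm). The utility SD, the correlations and their exchangeable form are all assumptions.

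Two stronger readings go too far. One is that the plan will produce a spurious QALY gain. Chance imbalance is as likely to produce a loss, and the unadjusted estimate is unbiased over repeated randomisation; the cost is lost precision and error conditional on the imbalance that happens to occur. The other is that imbalance could reverse the ICUR. The article gives no expected QALY effect, so the shift cannot be compared with one.

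**What to change.** Add to the cost-utility paragraph under Statistical analysis that incremental QALYs will be estimated by regression on arm, baseline EQ-5D-5L utility and the two stratification factors (self-reported prognosis and distress severity). The regression should be fitted within each imputed dataset and bootstrap replicate, and the adjusted differences should feed the ICUR, the cost-utility plane and the acceptability curves. If an analysis plan already says this, a confirming sentence is enough.

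Adjusting incremental costs for baseline costs, and estimating costs and QALYs jointly by seemingly unrelated regressions, are reasonable companions but optional; other specifications would also serve.

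The cost is a sentence in the plan and a few lines of code. No new data, visits or patients are needed, since EQ-5D-5L is already completed at baseline.
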